## Abstract

**Background:**

Amyotrophic lateral sclerosis (ALS) is a devastating neurodegenerative disease characterized by progressive motor neuron degeneration, leading to severe functional decline and limited therapeutic options. While current pharmacological interventions such as Riluzole offer only modest benefits, there is a growing imperative to explore complementary rehabilitation strategies. Preclinical and neuroimaging evidence suggests that Tuina, a traditional Chinese manual therapy, may influence synaptic plasticity and integrity, offering a biologically reasonable mechanism for therapeutic benefit.

**Methods:**

This randomized controlled trial, approved by the Ethics Committee of Hubei Provincial Hospital of Traditional Chinese Medicine (Approval No. HBZY2022-C42-01), will use a 1:1:1 allocation to enroll 135 participants. Participants will be assigned to: (i) Tuina therapy plus oral Riluzole, (ii) sham Tuina plus oral Riluzole, or (iii) Riluzole alone. Interventions will last for 1 year. The primary outcome is the change in Amyotrophic Lateral Sclerosis Functional Rating Scale-Revised (ALSFRS-R) scores. Secondary outcomes include manual muscle test (MMT), modified Ashworth scale (MAS), forced vital capacity (FVC), vital capacity (VC), forced expiratory volume in 1 second (FEV1), FEV1/FVC ratio, peak expiratory flow (PEF), maximal voluntary ventilation (MVV), and ALS Assessment Questionnaire (ALSAQ-40). Outcomes will be assessed at baseline, 4 weeks, and every 6 months up to 24 months. A mechanistic substudy will employ presynaptic Synaptic vesicle protein 2A (SV2A) PET imaging to quantify synaptic changes associated with Tuina intervention.

**Discussion:**

This study is designed to evaluate the clinical efficacy of Tuina therapy combined with Riluzole and to investigate its potential to modulate synaptic integrity in patients with ALS. The findings are expected to provide evidence for integrating Tuina as an adjunctive, non-pharmacological therapy into comprehensive ALS management, linking functional improvements to underlying synaptic mechanisms.

**Clinical trial registration:**

https://www.chictr.org.cn, identifier ChiCTR2300068650

## Introduction

1

ALS is a persistently progressive and fatal neurodegenerative disease marked by the degeneration of both upper and lower motor neurons in the motor cortex, brainstem, and spinal cord (1). This neuronal loss results in characteristic symptoms such as progressive muscle weakness, atrophy, fasciculations, and spasticity, ultimately leading to profound impairment of voluntary muscle control (2). A comprehensive systematic review identified 6,238 articles, of which 140 met the inclusion criteria for data extraction. Among these, 85 studies reported ALS incidence and 61 reported prevalence. The incidence rates varied widely, ranging from 0.26 to 23.46 per 100,000 person-years, with the lowest observed in Ecuador and the highest in Japan. Point prevalence ranged from 1.57 to 11.80 per 100,000 individuals. Notably, many of the included studies employed multiple data sources to enhance case ascertainment and diagnostic accuracy (3).

The rapid and progressive decline in motor function in ALS patients profoundly impairs their capacity to perform basic activities of daily living, including washing, dressing, and ambulation, ultimately leading to a marked loss of independence and a significant deterioration in quality of life (QoL) (4). As the disease advances, involvement of the respiratory muscles becomes inevitable, with respiratory failure representing the primary cause of mortality in affected individuals (5). Additionally, swallowing impairment (dysphagia) is a hallmark feature of ALS. Dysphagia develops in more than 85% of patients and contributes to malnutrition, dehydration, aspiration and poor quality of life (6, 7).

Despite decades of investigation, the etiology of ALS remains largely elusive, and no curative treatment has been identified (8). Current pharmacological options, such as Riluzole, and Edaravone offer only modest benefits, primarily in slowing disease progression and extending survival by a few months (9, 10). Diagnostic delays in ALS are substantial, with a median lag of 10 to 16 months from symptom onset to confirmed diagnosis—equating to nearly one-third of a patient’s remaining lifespan (11). This delay exposes individuals to accelerated motor decline, reducing their ability to perform essential daily tasks such as dressing, bathing, and ambulating, and severely compromising both their quality of life and autonomy (12).

These findings underscore Tuina’s potential as a valuable therapeutic modality in the context of neurodegenerative diseases and neurological recovery. By stimulating peripheral and segmental neural circuits, Tuina may exert neuroregulatory effects that support motor neuron integrity and mitigate functional decline. Tuina may support synaptic integrity and circuit-level plasticity in motor networks, precisely the domains affected in ALS. By integrating mechanistic neuroimaging modalities, especially SV2A PET, this trial is uniquely positioned to determine whether Tuina can promote presynaptic structural changes alongside clinical improvements.

## Objectives and hypothesis

2

Given the rapidly progressive nature of ALS and the limited benefits of current pharmacological interventions, there is an urgent need for adjunctive strategies that may preserve function and improve patient quality of life. Tuina has been proposed as a supportive intervention that may influence neuromuscular performance and central neural function.

The primary objective of this trial is to evaluate whether Tuina therapy combined with Riluzole can slow the decline of physical function in patients with early-stage ALS, as assessed by changes in the ALSFRS-R. Secondary objectives include determining the impact of the combined intervention on respiratory capacity, muscle strength, spasticity, and quality of life, as well as assessing the overall safety and tolerability of repeated Tuina sessions. Beyond clinical outcomes, the trial will also explore potential neurobiological mechanisms of Tuina. Using presynaptic SV2A PET imaging at baseline and 6 months, the objective is to examine whether functional changes are accompanied by preservation or enhancement of synaptic integrity in motor system regions.

It is hypothesize that Tuina combined with Riluzole will significantly slow functional decline and improve quality of life compared with Riluzole alone or sham Tuina plus Riluzole. Furthermore, it is anticipated that these clinical benefits may be linked to measurable synaptic changes, providing mechanistic evidence for Tuina as a complementary therapy in ALS.

## Methods and analysis

3

### Study design

3.1

This study is designed as a prospective, parallel-group, randomized controlled trial with a three-arm comparative design. Patients with ALS are identified and enrolled through systematic screening at the Hubei Provincial Hospital of Traditional Chinese Medicine. Recruitment began in September 2024 and is ongoing. Eligible participants will be randomly assigned in a 1:1:1 ratio to one of three groups: (i) Tuina therapy combined with Riluzole, (ii) sham Tuina therapy combined with Riluzole, or (iii) Riluzole alone. Randomization is performed using a computer-generated sequence created by an independent statistician not involved in participant recruitment or outcome assessment. Allocation is concealed using sequentially numbered, opaque, sealed envelopes (SNOSE) prepared prior to enrollment, and the envelopes are opened only after completion of baseline assessments to minimize selection bias.

All participants continue to receive standard pharmacological treatment with oral Riluzole throughout the trial. The intervention group receives a structured program of Tuina therapy, while the control group receives sham Tuina matched in duration and frequency. The standard care group receives Riluzole only. Interventions are delivered over a total treatment period of 12 months, beginning with a 4-week intensive phase followed by a maintenance schedule. Clinical efficacy and safety outcomes are assessed at baseline, after the 4-week intensive phase, and at Months 6, 12, 18, and 24. A mechanistic substudy employs presynaptic SV2A PET imaging at baseline and Month 6 to explore synaptic integrity changes associated with Tuina. A schematic flowchart is presented in Figure 1, and the study timeline is summarized in Table 1.

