**Figure 1 fig1:**
[figure not shown]
CONSORT flowchart illustrating the stages of the study, including screening, baseline data collection, randomization, outcome assessment, follow-ups, and analysis.

**Table 1 tab1:** Study design timeline illustrating enrollment, allocation, interventions, and outcome measurements at specified time points.

Time point	Enrollment	Allocation	Outcome measurement				
		Week 0	4 Weeks	6 Months	12 Months	18 Months	24 Months
Enrollment							
Eligibility screen	●						
Informed consent	●						
Allocation		●					
Interventions							
Riluzole		●	●	●	●	●	●
Tuina therapy		○	○	○	○	◎	◎
Assessments							
Baseline characteristics		●					
ALSFRS-R		●	●	●	●	●	●
Pulmonary function test		●	●	●	●	●	●
MMT		●	●	●	●	●	●
MAS		●	●	●	●	●	●
ALSAQ-40		●	●	●	●	●	●
Adverse event monitoring		●	●	●	●	●	●
PET		●	◎	●	◎	◎	◎

● Common in both groups. ○ Experimental group only. ◎ Neither in two groups.

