### Interventions

3.4

All participants, regardless of group allocation, will continue standard pharmacological treatment with oral Riluzole at a dose of 50 mg twice daily throughout the study period. Participants in the intervention arm will additionally undergo a structured program of Tuina therapy. This program will consist of sessions delivered over 12 consecutive months (five sessions per week). Each session will last approximately 45 min and will be administered by a certified senior Tuina therapist.

A tailored approach to Tuina therapy is essential for addressing the specific neuromuscular impairments associated with different segments of the body. According to the neuromuscular segmental localization principle in both traditional Chinese medicine and modern neuroanatomy, Tuina therapy can be strategically applied to areas where damage to motor neurons or muscular function occurs. By focusing on specific segments of the body, Tuina can provide precise stimulation that targets the dysfunction of corresponding spinal segments or neuroanatomical regions, optimizing therapeutic outcomes.

In Chinese medicine, this concept of segmental damage aligns with the idea that Qi and blood flow in specific meridians or channels are disrupted as a result of nerve dysfunction. The motor innervation corresponding to each spinal segment directly influences the muscles and joints within its dermatome or myotome. Thus, Tuina can be applied in a targeted manner to specific body segments corresponding to the site of neuronal damage, enhancing the treatment’s efficacy. Tuina therapy should be performed with a focus on the specific body segment affected by ALS, based on the neurological localization of motor neuron degeneration. The following table outlines common neuromuscular segments typically involved in ALS and the corresponding Tuina techniques (Table 2).

**Table 2 tab2:** Tuina therapy techniques for addressing neuromuscular impairments in ALS patients.

Step	Technique	Area of focus	Purpose	Description
1	Head and neck massage	Head, neck, face	Relieve tension	Gentle pressure on key acupoints like Yintang (between the eyebrows), Taiyang (temple), and Fengchi (back of the skull). This promotes blood circulation to relieve headache, tension, and improve neurological function.

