### Adverse events

3.7

In accordance with International Conference on Harmonization (ICH) Good Clinical Practice guidelines, a serious adverse event (SAE) is defined as any untoward medical occurrence that results in death, is life-threatening, requires inpatient hospitalization or prolongation of existing hospitalization, results in persistent or significant disability/incapacity, or leads to a congenital anomaly or birth defect. Any other medically significant event that may jeopardize the patient, or may require medical or surgical intervention to prevent one of these outcomes, will also be classified as an SAE.

Patient safety will be closely monitored throughout the study. Safety assessments will include routine physical examinations, monitoring of vital signs, laboratory tests, and 12-lead electrocardiograms (ECGs). All adverse events (AEs), regardless of severity, duration, or suspected relationship to study intervention, will be systematically documented in the electronic case report form (eCRF), reviewed by the investigator, and followed until resolution or stabilization. All SAEs will be reported promptly to the Ethics Committee in compliance with regulatory requirements and institutional policies. The Data and Safety Monitoring Board (DSMB), where applicable, will periodically review safety data to ensure ongoing participant protection.

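### Adverse event comparisons with riluzole alone are open to ascertainment bias, because two arms have frequent therapist sessions, the third has none, and scheduled safety visits are up to six months apart

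*Protocol article*

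**What the plan says.** Objectives and hypothesis (2) lists several secondary aims, "as well as assessing the overall safety and tolerability of repeated Tuina sessions".

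Study design (3.1) sets the timetable: "Clinical efficacy and safety outcomes are assessed at baseline, after the 4-week intensive phase, and at Months 6, 12, 18, and 24". In Table 1 the row "Adverse event monitoring" is marked at those same six time points. Adverse events (3.7) is broader. It says that safety is followed for the whole trial, and: "All adverse events (AEs), regardless of severity, duration, or suspected relationship to study intervention, will be systematically documented" in the eCRF.

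Planned contact differs by arm. Interventions (3.4) describes Tuina as "sessions delivered over 12 consecutive months (five sessions per week". Study design says of the second arm, "while the control group receives sham Tuina matched in duration and frequency", and of the third: "The standard care group receives Riluzole only".

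The session frequency is not consistent. Study design describes an intensive first four weeks and then maintenance at an unstated frequency, and Follow-up (3.5) refers to a four-week treatment phase. These passages must be reconciled with the five sessions a week in Interventions.

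**The concern.** An adverse event count depends on how often events occur and on how often someone is in a position to hear about them. Here the second factor differs by arm. For up to a year, participants in two arms regularly meet a therapist to whom they can mention pain, bruising or fatigue. Those on riluzole alone have only the scheduled visits described in the article.

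The plan records every event but does not separate events sought in the same way in all arms from events that surface because a session took place. If both go into one table, part of any excess over riluzole alone may be an excess of opportunities to report. If instead only visit reports count, transient effects of manual therapy have to be recalled over many weeks, and the tolerability aim loses the events it most needs. Events not asked about at the time cannot be recovered at analysis, and recruitment is already under way.

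**Working it through.** The plan gives no figure for adverse event detection, so there is none to reproduce.

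**1. Planned contact in the treatment year**
- Safety visits after baseline, all arms: week 4, month 6 and month 12, so 3.
- Sessions in the Tuina and sham arms, if five per week holds throughout: 5 × 52 = 260.
- Week 4 to month 6: about 26 − 4 = 22 weeks, or 22 × 5 = 110 sessions.
- Month 6 to month 12: about 26 weeks, or 26 × 5 = 130 sessions.
- If five per week applies to the first four weeks only: 5 × 4 = 20 sessions plus an unstated number of maintenance sessions.
- Riluzole alone: 0 sessions on any reading.
- After month 12 Table 1 shows no Tuina, so planned contact is equal again.

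**2. If session-reported events enter the record**

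Assume the same true proportion p of participants with an event in both arms. Let capture be 0.95 in a session arm and c under riluzole alone. The observed ratio is (0.95 × p)/(c × p) = 0.95/c, whatever p is:
- c = 0.80: 1.19
- c = 0.60: 1.58
- c = 0.40: 2.37 (2.375 before rounding, hence the 2.4 in the summary)

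The chance of a false significant difference was found by exact binomial enumeration of a pooled two-sided z test at 0.05, with p from 0.2 to 0.6. Sample size (3.2) gives 45 recruited and 36 evaluable per arm (36/0.8 = 45).

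| Capture, session arm v riluzole alone | Spurious ratio | 45 per arm | 36 per arm |
|---|---|---|---|
| 0.95 v 0.95 | 1.00 | about 5% | about 5% |
| 0.95 v 0.80 | 1.19 | 7% to 13% | 6% to 11% |
| 0.95 v 0.60 | 1.58 | 16% to 50% | 13% to 42% |
| 0.95 v 0.40 | 2.37 | 35% to 90% | 29% to 83% |

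The capture rates, p and the choice of test are all assumptions; none comes from the document. The first row is what equal enquiry would give. It also describes Tuina versus sham, if equal contact means equal capture.

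**3. If only visit reports count**

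All three arms are asked at the same visits over the same recall interval. With equal capture c the expected ratio is (c × p1)/(c × p2) = p1/p2, so it is preserved. The difference becomes c × (p1 − p2). At the assumed c of 0.40 to 0.80, 20% to 60% of events are lost in every arm, and a true excess shrinks by the same fraction. This is under-counting, not inequality between arms.

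**The case against.** The strongest reply is that the protocol does not confine safety to visits. Adverse events (3.7) describes monitoring for the whole trial, Data management (3.9) adds continuous monitoring and a monitoring committee, and the columns of Table 1 are visits, so it could not show reporting between them. This stands: a reader might infer from the timetable that adverse events are collected only at visits, and the text does not support that. But ongoing reporting without a common enquiry is the case in which unequal contact matters, and a committee reviewing accumulated data cannot correct unequal collection.

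Second, a reader might infer that the safety objective cannot be answered without bias. That is too strong. The objective concerns Tuina sessions, and sham participants have the same planned contact, so Tuina versus sham is balanced in this respect. Two limits remain: that contrast cannot show harms of attendance or handling common to both arms, and Limitations (6) concedes that blinding of participants and therapists is incomplete, so reporting could still differ.

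Third, the details of adverse event enquiry often sit in a full protocol that an article condenses. Their absence here is not the point. The point rests on what the article does fix: the visit timetable, the unequal session contact, and the documentation of all events.

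**Conclusion.** The point holds as a conditional risk. If events raised at sessions enter the record, comparisons of event frequency with riluzole alone are open to ascertainment bias during the treatment year, chiefly for mild and transient events. Deaths and hospital admissions are less exposed. If only visit reports count, such events are under-counted in all arms alike. Tuina versus sham is not distorted by unequal contact.

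A reader might take the ratios of 1.2 to 2.4, or the false-significance rates, as estimates for this trial, or conclude that events are in fact being found unequally. The document supports neither. It gives no capture rates and names no specific test for adverse events. The size of the contact imbalance is also uncertain until the session frequency is reconciled, and 95% capture might not hold at a lower maintenance frequency. The direction of the imbalance does not change: any maintenance schedule leaves riluzole alone with less contact.

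**What to change.** - In 3.7 and Table 1, state one scripted adverse event enquiry given at the same times in all three arms. The minimum is every scheduled visit; preferably add a short periodic call during the treatment year by the follow-up nurse already named in Follow-up (3.5).
- Continue to document every event, but record its source. Use only events from the common enquiry for comparisons involving riluzole alone.
- Record session-reported events, and stopped or missed sessions with reasons, on the session checklist already used for treatment fidelity. Compare these between Tuina and sham only, and name that as the main safety and tolerability contrast, noting that it cannot show harms common to both.
- Reconcile the statements on session frequency in 3.1, 3.4 and 3.5.

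Cost: an amendment to 3.7 and Table 1, an added checklist entry, some nurse time if calls are added, and more minor events recorded under riluzole alone. The first option, enquiry at existing visits, needs no new staff or contacts but leaves the six-month recall in place; the calls shorten it. Neither changes treatment, eligibility or the primary endpoint.

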**Figure 1 fig1:**
[figure not shown]
CONSORT flowchart illustrating the stages of the study, including screening, baseline data collection, randomization, outcome assessment, follow-ups, and analysis.

**Table 1 tab1:** Study design timeline illustrating enrollment, allocation, interventions, and outcome measurements at specified time points.

Time point	Enrollment	Allocation	Outcome measurement				
		Week 0	4 Weeks	6 Months	12 Months	18 Months	24 Months
Enrollment							
Eligibility screen	●						
Informed consent	●						
Allocation		●					
Interventions							
Riluzole		●	●	●	●	●	●
Tuina therapy		○	○	○	○	◎	◎
Assessments							
Baseline characteristics		●					
ALSFRS-R		●	●	●	●	●	●
Pulmonary function test		●	●	●	●	●	●
MMT		●	●	●	●	●	●
MAS		●	●	●	●	●	●
ALSAQ-40		●	●	●	●	●	●
Adverse event monitoring		●	●	●	●	●	●
PET		●	◎	●	◎	◎	◎

● Common in both groups. ○ Experimental group only. ◎ Neither in two groups.

### Sample size

3.2

The sample size calculation was primarily based on the ALSFRS-R as the main clinical endpoint, reflecting the study’s primary objective to evaluate functional decline. Calculations were performed using G*Power software (version 3.1.9.7) for an F-test. Based on a projected medium effect size (*f* = 0.35) for the ALSFRS-R, derived from prior research and clinical expectations for interventions in ALS, a statistical power of 90% (1-*β* = 0.9) and a significance level of *α* = 0.05 across three groups, a total sample size of 108 participants was determined to be necessary. This calculation yields an actual power of approximately 0.905, ensuring sufficient power to detect a clinically meaningful effect on the primary outcome.

To account for the inherent heterogeneity of ALS and to enhance the ability to detect moderate effect sizes and explore potential subgroup differences, the final recruitment target has been further adjusted. Considering an anticipated dropout rate of approximately 20% over the 12-month treatment and follow-up period, the required effective sample size of 36 participants per group (108 participants total) necessitates recruiting 45 participants per group. Thus, the total recruitment target for the study is 135 participants (45 participants × 3 groups). This increased recruitment target ensures that, even with expected attrition, the study will retain sufficient power for the primary outcome and will also allow for more reliable detection of moderate effect sizes, thereby enhancing the precision of exploratory subgroup analyses in this complex disease.

